#### Strategies to improve adherence to interventions {11c}

Participants adherence with the assessment schedules of the two EMA periods and the EMI will be monitored electronically by the research team, using the administration tool of the web-based software program ASMO. Participants showing a significant drop in their response rate will be contacted to clarify the reasons of non-adherence, boost motivation, and offer problem-solving and support when needed.

A high standardization of the introduction and closing sessions will be facilitated by the usage of a detailed session manual and intensive training and supervision of the researchers conducting the session.

#### Relevant concomitant care permitted or prohibited during the trial {11d}

Individuals who already receive psychological therapy that specifically targets hearing voices (e.g., face-to-face CBTp) cannot participate in the study. No other restrictions are imposed on the TAU.

#### Provisions for post-trial care {30}

Participants who are not yet receiving standard treatment and who express an interest in it at the end of the study will receive information about suitable mental health services in the area where they live.

In the unlikely event of study-related damages or injuries, the liability of the Universitären Psychiatrischen Dienste (University Psychiatric Services) Bern, Switzerland, will provide compensation, except for claims that arise from misconduct or gross negligence.

### Outcomes {12}

The primary outcome of the study is the change in the Distress dimension of the Psychotic Symptom Rating Scales Auditory Hallucinations subscale (PSYRATS-AH) [30] between the baseline (T0) and the 3-month follow-up (T1) assessments. Reducing the level of psychological distress due to voice-hearing (instead of reducing hearing voices per se) is the main therapy aim of CBTv and the PSYRATS-AH has been widely used in clinical trials investigating the efficacy of CBTv in the past [17, 35, 36]. Additionally, distress is the prioritized outcome by patients with voices and is related to dysfunction [37].

Secondary outcomes of the study include the change in (1) voice-related distress (distress dimension of the PSYHRATS-AH) between T0 or T1 and the 6-month follow-up (T2); (2) perceived hostile intent and power of voices (Persecutory Beliefs subscale of the Revised Beliefs About Voices Questionnaire; BAVQ-R) [38]; and (3) perceived voice dominance and intrusiveness (Voice and You-Revised; VAY-R) [39], passive, aggressive, and assertive relating to voices (Approve questionnaires) [40], and negative core beliefs about the self (Brief Core Schema Scales, BCSS) [41] between T0, T1, and T2. Appraisals of and relating styles to voices as well as core beliefs about the self were chosen as secondary outcomes because they represent potential mediators of the efficacy of the CBTv-based EMI [35, 42].

Other outcomes include changes in (1) severity of depression, anxiety, and stress (Depression, Anxiety and Stress Scale-21 (DASS-21) [43]); (2) overall illness severity (Clinical Global Impression Scale-Severity (CGIs) [44]); (3) psychosocial functioning (Social and Occupational Functioning Assessment Scale (SOFAS) [45]); and (4) quality of life (Quality of Life Enjoyment and Satisfaction Questionnaire (Q-LES-Q-18) [46]) between T0, T1, and T2.

### Participant timeline {13}

The participant timeline is depicted in Fig. 1 and will be reported in line with the Consolidated Standards of Reporting Trials 2013 statement [47].

### Sample size {14}

Sample size calculation was based on the expected difference between the TAU + CBTv-based EMI group and the TAU group in the severity of the PSYRATS-AH Distress dimension between the baseline (T0) and the 3-month follow-up (T1) assessments. Pilot studies examining the efficacy of the CBTv that is adopted for use as EMI in the current trial reported large effect sizes (Cohen’s *d* ranging between 1.3 and 1.78) [35, 42]. Given that these studies involved face-to-face therapy and that effect sizes are likely to be reduced in a full-scale trial, a medium effect size is targeted in the current study. A power-analysis for an analysis of variance with two groups (TAU + CBTv-based EMI, TAU), and two repeated measures (T0, T1) and within-between interaction (group x time), was calculated using G*Power 3.1.9.4 [48]. Assuming a medium effect size of *f* = 0.25, a power of 0.80, and an alpha level of .05, a sample size of *N* = 128 is required. Including an expected attrition rate of 20%, the required total sample size for the RCT is *N* = 154, with 77 participants in each treatment arm.

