## Discussion

This is the first study to examine the efficacy of CBTv, delivered using smartphone-based EMI in a transdiagnostic sample of youth with distressing voices. The study helps to bridge several clinical and scientific gaps. Clinically, it provides a highly specialized, low-intensity and flexible treatment opportunity for a hitherto neglected patient group for whom specialized treatment has been scarce and who are known for their low engagement with conventional mental health services. Thus, the trial has the potential to make a significant contribution to early intervention in order to prevent negative long-term outcomes and improve the life trajectories of the affected young people. Scientifically, the study will contribute to clarify whether CBTv is suitable for young voice-hearers and for voice-hearers without a psychotic disorder, whether CBTv can be successfully delivered using smartphone-based EMI, what the mechanisms of change through therapy are, and who benefits from therapy and who does not.

Despite these benefits, the following limitations of the study design have to be acknowledged. First, the EMI is based on CBTv that was recently developed for adults with distressing voices and has been evaluated in patients with primarily psychotic disorders so far. Any change to an existing therapy in terms of content, format, or target group involves the risk that it is no longer or less effective. Second, the definition of TAU as including both receiving no psychiatric/psychological treatment at all and any form of psychiatric/psychological was chosen to make the intervention accessible to as many young people as possible, but creates the disadvantage of the TAU being heterogeneous. Third, reaching the target number of 154 participants for the trial may be challenging. However, the risk of low recruitment numbers is addressed through the multicenter approach. Finally, e-mental health interventions are less obliging than traditional face-to-face treatments and may therefore suffer from lower adherence and higher drop-out rates. The research team will pay special attention to keeping participants in the study. In addition, participants will be overrecruited to compensate for a dropout rate of up to 20%.

If the present study is successful despite the discussed potential challenges, it may make a significant contribution to early intervention for young people with distressing voices.

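### The 20% attrition allowance was applied as 128 × 1.2 rather than 128 / 0.8, so 154 participants cover attrition only up to 16.9%

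*Protocol article*

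**What the plan says.** The Sample size section ({14}) of the protocol article bases the calculation on an analysis of variance with two groups and "two repeated measures (T0, T1) and within-between interaction (group x time), was calculated using G*Power 3.1.9.4". The target is a medium effect of f = 0.25, with "a power of 0.80, and an alpha level of .05, a sample size of" 128. The next sentence adds the allowance for loss: "Including an expected attrition rate of 20%, the required total sample size for the RCT is" "154, with 77 participants in each treatment arm".

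The Discussion repeats the purpose of the extra recruitment: "participants will be overrecruited to compensate for a dropout rate of up to 20" per cent. The Abstract also gives the total of 154. The article offers no other formula or reason for that number.

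**The concern.** An attrition rate is a proportion of the people who enter the trial. If 128 must remain after 20% are lost, the number to randomize is 128 divided by 0.80. Multiplying 128 by 1.20 answers a different question, because the 20% is then a share of the completers, and the result is always too small. The figure 154 looks like the product of that multiplication.

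If so, the five stated planning values (f = 0.25, power 0.80, alpha .05, 20% attrition, total 154) do not fit together under the article's own calculation, and the Discussion promises more protection against dropout than the sample size gives. The point has some practical weight because the Discussion itself warns that digital interventions may have higher dropout than face-to-face treatment. Attrition near 20% is therefore within what the investigators expect.

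**Working it through.** **Inputs** (all from Sample size {14}, except the allocation ratio from Trial design {8})
- Effect size f = 0.25, equivalent to d = 0.50 for two equal groups
- Alpha .05; the F test is non-directional
- Power 0.80
- Number required before attrition: 128 (64 per arm at 1:1)
- Attrition: 20%
- Stated total: 154 (77 per arm)

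**Step 1: reproduce 128.** For the group × time test with two groups and two times, the F statistic has 1 and N − 2 degrees of freedom. With noncentrality λ = f² × N = 0.0625 × N:
- N = 128: λ = 8.0, power = 0.8015.

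This is the smallest even N that reaches 0.80, so the base figure is reproduced and is not in question here. It corresponds to the software's Cohen-type effect-size option. The alternative option, which uses the correlation between repeated measures, gives 34 at a correlation of 0.5 or 66 at 0, and neither matches.

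**Step 2: reproduce 154.**
- 128 × (1 + 0.20) = 153.6, rounded up to 154. This matches the article.
- 128 / (1 − 0.20) = 160, or 80 per arm. This does not match; the gap of 6 is too large for rounding.

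**Step 3: what 154 delivers at 20% attrition.**
- 154 × 0.80 = 123.2 remaining, which is 4.8 short of 128.
- N = 123: λ = 0.0625 × 123 = 7.69, power = 0.785.
- The variant λ = f² × (N − 2) gives 0.779 at N = 123. That variant would have needed 130 rather than 128, so it is not the one the article used.
- The effect detectable with 80% power rises from d = 0.50 to about d = 0.51.

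**Step 4: what attrition 154 does cover.**
- 1 − 128/154 = 0.1688, so at most 16.9%.

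**Step 5: check of the correct form.**
- 160 × 0.80 = 128 remaining, power = 0.8015.

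| Total randomized | Left after 20% loss | Power at f = 0.25 |
|---|---|---|
| 154 (stated) | 123.2 | 0.785 (N = 123) |
| 160 | 128 | 0.8015 |

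**The case against.** Nobody can defend 154 as the output of the stated calculation, but there are three fair arguments that it matters little.

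*The planned analysis is not the planning test.* The Statistical methods section ({20a}) specifies a multilevel model that uses all available data and includes baseline distress as a fixed effect. Suppose f refers to the T0–T1 change contrast and the model acts as a baseline-adjusted comparison at T1. The error variance is then that of the change score times (1 + ρ)/2, where ρ is the T0–T1 correlation. The article gives no ρ. Taking a range as an assumption, power with 123 participants would be about 0.93 at ρ = 0.3, 0.89 at 0.5, 0.85 at 0.7 and 0.81 at 0.9, and would fall below 0.80 only above roughly 0.93. Participants seen at T2 but not at T1 would also add a little information. This is a good reason not to fear for the trial's real power. It does not repair the calculation: the article makes no such argument for 154, and the wording of the model leaves open whether it works in that way.

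*The 20% may refer to the whole study.* Neither place ties it to T1, and follow-up runs to T2. If no more than 16.9% were lost by T1, 154 would be enough. However, the calculation that receives the allowance is for T0 to T1, so the natural reading is loss by T1.

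*The size is trivial.* The loss is about 1.5 power points and the detectable effect shifts by 0.01 in d, for a target that is itself a conventional medium value. This stands. It bears on how serious the error is, not on whether there is one.

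Reading the 20% as an over-recruitment percentage fails, because the two sections call it an attrition rate and a dropout rate.

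**Conclusion.** The concern holds. The stated total of 154 results from applying the 20% to the wrong base; with 128 needed after a 20% loss, the total is 160. On the article's own planning test, 154 gives power of about 0.785 at 20% attrition and keeps 80% power only up to 16.9%. The Discussion's statement about compensating for up to 20% is therefore not met by the calculation offered for it.

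The error is definite but its effect is minor: six participants and about 1.5 points of power, with no bearing on bias or type I error. The conclusion assumes that 128 analysable participants at T1 are required, as the article says, and that the 20% is loss by T1. The power actually achieved may be higher under the baseline-adjusted multilevel model, but this cannot be quantified from the article.

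**What to change.** Keep 154 and correct the text in Sample size {14} and in the Discussion. One of two statements will do:
- 154 participants retain 80% power for attrition of up to 16.9%; or
- with 154 participants and 20% attrition, about 123 remain and power is about 0.79 at f = 0.25.

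The same statement should appear in both sections. The total in the Abstract then needs no change. The cost is two sentences and a slightly less favourable stated power or attrition tolerance; recruitment, conduct and analysis are untouched.

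Raising the total to 160 (80 per arm) would also make the figures agree. It is a real cost, however, because it means six more participants in a trial whose Discussion already describes reaching 154 as a possible difficulty. A loss of this size does not call for it.

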### Recruitment {15}

Participants will be recruited through referrals from clinical practitioners from the host clinics and clinical psychologists and psychiatrists in private practice as well as via the webpage www.online-therapy.ch from the University of Bern, internet forums, and advertisements in print and social media.

## Assignment of interventions: allocation

### Sequence generation {16a}

Randomization will be performed by the biostatistician of the University Hospital for Child and Adolescent Psychiatry and Psychotherapy, University of Bern, Switzerland (SL). Minimization, a covariate adaptive randomization, will be applied, which sequentially assigns each new participant to one of the two treatment arms by taking into account previous assignments of participants and specific covariates. This method ensures balance in important prognostic factors without the pitfalls of stratified randomization [49]. Imbalance is calculated according to Pocock and Simon [50]. In this trial, minimization will balance whether (a) voices are experienced daily or not (PSYRATS-AH item 1 (frequency) score 1 versus ≥2) and (b) participants receive any psychiatric/psychological treatment or not, because these variables are predicted to have an effect on treatment response and should therefore be balanced across groups.

### Concealment mechanism {16b}

The baseline data of each new participant including the covariates that will be used for randomization will be entered into REDCap (Research Electronic Data Capture) hosted at the University Bern, Switzerland [51, 52] (see below for more information on data management using REDCap). The data will then be exported by the biostatistician of the University Hospital for Child and Adolescent Psychiatry and Psychotherapy, University of Bern, Switzerland (SL), to STATA 17 [53]. He will allocate new participants to TAU + CBTv-based EMI or TAU based on the algorithm described by Pocock and Simon [50]. The treatment assignment will be entered by the biostatistician into REDCap in a manner that is hidden from the blinded assessors.

### Implementation {16c}

The principal investigator (MC) will be notified by the biostatistician (SL) about a participant’s group allocation. The principal investigator will then inform the member of the research team (JK) who is responsible for forwarding the information to the participant and conduct the introduction and closing sessions for those allocated to the TAU + CBTv-based EMI group.

## Assignment of interventions: blinding

### Who will be blinded {17a}

Members of the research team who will conduct the 3-month (T1) and the 6-month follow-up (T2) assessments will be blinded. Success of blinding will be assessed by asking researchers conducting T1 and T2 assessments to guess which condition the participant was allocated to and indicate their confidence. It is not feasible to blind participants to their allocation due to the design of the trial. Participants will be asked not to reveal their group allocation to the researcher conducting the T1 and T2 assessments. Additionally, researchers conducting the T1 and T2 assessments will be shielded from discussion of participants. Accidental unblinding of researchers conducting the T1 and T2 assessments will be recorded and addressed by repeating the assessment as soon as possible by another blind researcher. The principal investigator (MC) will not be blinded and will respond to any clinical or research issues during the trial that require knowledge of a participants’ group allocation.

### Procedure for unblinding if needed {17b}

There are no circumstances under which unblinding of researchers conducting the T1 and T2 assessments is permissible.

## Data collection and management

### Plans for assessment and collection of outcomes {18a}

Table 1 gives an overview about the diagnostic interviews and questionnaires and the assessment schedule.

**Table 1 Tab1:** Assessment schedule

		T0	T1	T2
Interviews	Demographic information	x		
	Characteristics of the TAU	x	x	x
	Structured Interview for Psychosis-Risk Syndromes (SIPS)	x		
	Structured Clinical Interviews for Mental Disorders (DIPS)/Structured Clinical Interview for Mental Disorders in children and adolescents (Kinder-DIPS)	x		
	Module B (psychotic disorders) of the Structured Clinical Interview for DSM-5 Disorders—Clinician Version (SCID-5-CV)	x		
	BPD module of the Structured Clinical Interview for DSM-5 Personality Disorders (SCID-5-PD)	x		
	Psychotic Symptom Rating Scales Auditory Hallucinations subscale (PSYRATS-AH)	x	x	x
	Clinical Global Impression Scale-Severity (CGIs)	x	x	x
	Social and Occupational Functioning Assessment Scale (SOFAS)	x	x	x
Questionnaires	International Trauma Questionnaire (ITQ)/International Trauma Questionnaire—Child and Adolescent version (ITQ-CA)	x		
	Child and Adolescent Trauma Screen (CATS)	x		
	Childhood Trauma Questionnaire (CTQ)	x		
	Dissociation Tension Scale (DSS)	x		
	Revised Beliefs About Voices Questionnaires (BAVQ-R)	x	x	x
	Voice and You—Revised (VAY-R)	x	x	x
	Approve questionnaires	x	x	x
	Brief Core Schema Scales (BCSS)	x	x	x
	Depression, Anxiety and Stress Scale-21 (DASS-21)	x	x	x
	Quality of Life Enjoyment and Satisfaction Questionnaire (Q-LES-Q-18)	x	x	x
	Treatment satisfaction questionnaire		x	

#### Eligibility screening

The eligibility screening is informed by the PSYRATS-AH [30]. A description of the measure is given below.

#### Measures to characterize the sample

##### Sociodemographic information

This interview assesses sociodemographic variables such as age, gender, current education or employment, living situation, relationship status, and income.

##### Clinical information

Detailed information on psychiatric disorders in first-degree relatives, the treatment history, and the type and extent of the TAU will be obtained in a structured way.

##### Structured interview for Psychosis-Risk Syndromes (SIPS) [54]

The SIPS is a commonly used instrument to assess clinical high-risk (CHR) syndromes for psychosis. The SIPS includes a 19-item severity scale, the Scale Of Psychosis-risk Symptoms (SOPS), that measures five positive, six negative, four disorganization, and four general symptoms, each scored from 0 (absent) to 6 (severe and psychotic). Participants meet threshold for a SIPS-defined risk syndrome or a first-episode psychosis based on their score on one or more positive symptoms. High predictive validity and interrater reliability have been reported [55].

##### Diagnostic Interview for Mental Disorders (Diagnostisches Interview bei Psychischen Störungen; DIPS) [56]/Diagnostic Interview for Mental Disorders in Children and Adolescents (Diagnostisches Interview bei Psychischen Störungen im Kindes- und Jugendalter; Kinder-DIPS) [57]

The DIPS interviews are structured clinical interviews to assess mental disorders in adults (≥ 16 years of age) and children/adolescents (6–18 years of age), respectively, according to the ICD-10 and DSM-5. While the Kinder-DIPS includes two parallel versions for children/adolescents and their parents, only the former one will be applied in the current trial. Adequate validity and reliability have been reported for both the DIPS [58, 59] and the Kinder-DIPS [60–62].

##### Module B (psychotic disorders) of the Structured Clinical Interview for DSM-5 Disorders—Clinician Version (SCID-5-CV) [63]

Since the DIPS interviews contain only a brief screener for psychotic disorders, module B of the SCID-5-CV is applied to assess psychotic disorders according to the ICD-10 and DSM-5.

##### Borderline personality disorder (BPD) module of the Structured Clinical Interview for Personality Disorders (SCID-5-PD) [64]

The SCID-V-PD is a structured clinical interview for the detection of personality disorders according to the DSM-5. In the current trial, the BPD module will be administered as there is increasing evidence suggesting that hearing voices is a common phenomenon in individuals with BPD [65]. The BPD module examines the presence of the nine criteria for BPD defined by DSM-5. Each item is scored on a three-point scale (1=absent, 2=subthreshold, 3=present). The diagnosis requires that five or more criteria are met. A BPD criterion is scored as met if it has been present for 2 years for individuals older than 18 years, and for 1 year for under-age individuals [66]. The BPD module of the SCID-V-PD has been widely used in clinical and research settings for adults and has also been successfully adopted for the adolescent population [67].

##### International Trauma Questionnaire (ITQ) [68]/International Trauma Questionnaire—Child and Adolescent version (ITQ-CA) [69]

The ITQ and ITQ-CA are valid and reliable measures of ICD-11 posttraumatic stress disorder (PTSD) and Complex PTSD (CPTSD) for adults and children/adolescents (aged 7 to 17), respectively. They are included in the current trial, as evidence indicates that hearing voices is a common phenomenon in patients with trauma-related disorders [70, 71]. The ITQ measures will be used in conjunction with the traumatic events checklist of the *Child and Adolescent Trauma Screen (CATS)* [72]. The list includes 14 potentially traumatic experiences and participants are asked to indicate if they experienced any of those, using a binary “yes/no” response. If a participant experienced at least one traumatic event, the CATS will be followed by the ITQ or the ITQ-CA, respectively. The ITQ measures include 12 items reflecting symptoms of PTSD (i.e., re-experiencing, avoidance, sense of threat) and disturbances in self-organization (i.e., affective dysregulation, negative self-concept, disturbances in relationships). Participants indicate on a 5-point Likert-Scale ranging from 0 (never) to 4 (almost always) how much they have been bothered by each symptom over the past month. Scores of ≥ 2 (moderately) indicate the presence of a symptom. Additionally, five items assess functional impairment in different areas of life (e.g., friends, family, school, hobbies), using a binary yes/no scale. The presence of at least one symptom from each PTSD cluster and at least one indicator of functional impairment is required for a PTSD diagnosis. The presence of at least one symptom from each PTSD and disturbances in the self-organization cluster and at least one indicator of functional impairment is required for a CPTSD diagnosis. If participants meet the criteria for CPTSD, the PTSD diagnosis is excluded.

